## Methods

### Overview

VENT is a two-arm, randomized, controlled, multi-center trial designed to study the safety and efficacy of the EBV implantation procedure, and the ability of the EBV to produce sustained improvement of symptoms in emphysema. The study sample size was a minimum of 270 subjects with heterogeneous emphysema, with randomization at a ratio of 2 to 1 (*i.e., *two patients were randomized to the study device treatment arm for every one randomized to the control group).

Given the similarity in intended treatment effect between LVRS and EBV implantation, combined with a goal of allowing easy comparisons between the results of the NETT and VENT, the VENT design largely followed that of the NETT. The inclusion/exclusion criteria were similar and both studies required pulmonary rehabilitation prior to randomization in order to maximize function prior to intervention. Both studies allowed treatment of the upper or lower lobes based on CT analysis; however, the NETT required bilateral (left and right lung) treatment whereas VENT treatments were unilateral only. Patient randomization in VENT was stratified per the subgroups identified in the NETT according to lung treatment region (upper versus lower) and post rehabilitation pre-treatment exercise capacity (low versus high).

In addition, the VENT study design conformed to the consensus recommendations of an independent panel of physician specialists convened by the U.S. Food and Drug Administration in February of 2003 to provide study design input for emerging bronchoscopic treatments for emphysema[10]. Questions considered at the panel included appropriate control groups, safety assessment, appropriate outcome metrics, and length of follow up.

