The initial analysis will evaluate the mean percent change between EBV and control in FEV_1 _and 6 MWT using an unpaired t-test if data are normally distributed or Mann-Whitney-Wilcoxon test if data require non-parametric testing. To determine if covariates impact the primary outcome variables, and to adjust for potential imbalances in randomization, both primary endpoints will be further tested via a multivariate model (SAS PROC MIXED). In order to reduce the possibility of over-specification of the model, the potential covariates listed in Tables 6, 7, 8, 9 will be subjected to a univariate screening procedure similar to that described by Hosmer and Lemeshow[20]. Derivations for these variables are provided in Table 10. Main effects and interactions with a p-value of 0.15 or less are allowed to enter a multivariate analysis using a mixed linear model (SAS PROC MIXED). The treatment effect must remain in the model in order to substantiate the one-tailed test of superiority. Those variables found to have statistically significant interactions with the treatment arm via the mixed model analysis will be further analyzed in follow-on sub-group analyses. In order to limit the impact of multiple hypothesis testing, univariate sub-set analysis will be performed using only those independent variables that remain in the mixed model as interactions with the treatment arm. For those analyses performed on the remaining independent variables, appropriate adjustments will be made to account for impact on Type I error[11]. Secondary endpoint analyses will follow the same methodology as described above.

**Table 6 T6:** Plethysmography, spirometry and HRCT derived baseline potential covariates*

Variable	Plethysmography/Spirometry	HRCT at TLC	HRCT at RV	TLC and RV HRCT ^†^
RV	X			
RV % Predicted	X			
TLC	X			
TLC % Predicted	X			
RV/TLC	X			
VC	X			
FVC	X			
FVC % Predicted	X			
FEV_1_	X			
FEV_1 _% Predicted	X			
FEV_1_/FVC	X			
Destruction Score of Target Lobe		X	X	
Ipsilateral Heterogeneity^††^		X	X	
Whole Lung Heterogeneity^††^		X	X	
For RUL Treatment Subset only: RUL-RML Heterogeneity^††^		X	X	
Target Lobe Volume % of TLC		X		
Target Lobe Volume % of RV			X	
Max Destruction Score other than target		X	X	
Min Destruction Score other than target		X	X	
Target Lobe Destruction Score % TLC-RV Delta				X
Target Lobe Volume % TLC-RV Delta				X
Fissure Score^†††^		X		

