*Variables marked in multiple columns will be calculated twice, once using the expiratory (RV) CT and once using the inspiratory (TLC) CT. All tests are at Baseline.

^†^Some variables require information from both the TLC and RV CT

^†† ^Heterogeneity scores are derived by subtracting the minimum destruction score from the maximum destruction score.

^††† ^Fissure Score is an integer scale from one to three base on visual scoring by core center radiologists (1 = Fissure Absent, 2 = Incomplete Fissure, 3 = Complete Fissure).

**Table 7 T7:** Other baseline and procedure potential covariates

	Baseline	Procedure
Gender	X	
Age	X	
Site	X	
6 MWT	X	
Cycle Ergometry	X	
BMI	X	
DLCO % Predicted	X	
PaO_2_	X	
PaCO_2_		
Target Lobe		X
RUL Treatment		X
Upper vs. Lower		X
Right vs. Left		X
Valve Version*		X
Large Valve*		X
Small Valve*		X
Valve Combos*		X
Valve Expectorated*		X

*These potential covariates apply only to the treatment arm and do not have a control arm subset.

**Table 8 T8:** Composite or other potential covariate interactions

Composite or Interactions	Definition
Baseline BODE	BMI, FEV_1_% predicted, MMRC, 6 MWT Composite Score
NETT Strata	Randomization Stratification by Baseline Cycle Ergometry and HRCT at TLC
NETT Strata by Right vs. Left	Randomization Stratification by Baseline Cycle Ergometry and HRCT at TLC, by Right or Left Lung
Lobar Exclusion by Fissure Interaction*	Fissure Score = 3 AND Lobar Exclusion = Yes vs. all others
Lobar Exclusion, Fissure, and RV % Predicted*	Lobar Exclusion = Yes AND Fissure Score = 3 AND RV % Predicted ≥ 200% vs. all others
Lobar Exclusion, Fissure, and RV % Predicted*	Lobar Exclusion = Yes AND Fissure Score = 3 AND RV % Predicted ≥ 200% vs. all others
Large Valve by Right vs. Left*	Right vs. Left Lung AND Large Only vs. Others
Small Valve by Right vs. Left*	Right vs. Left Lung AND Small Only vs. Others
Expectorated Valve Replaced*	Valve(s) Expectorated AND Lobar Exclusion = Yes vs. all others
Expectorated Valve Not Replaced*	Valve(s) Expectorated AND Lobar Exclusion = No vs. all others
Lobar Exclusion by Site*	Technical Success by Site
First Case by Site*	First Treatment Case by Site vs. All Others
Learning Curve by Site*	Experience Level: Case 1, vs. 2 & 3, vs. 4–6, vs. 7–9, vs. ≥10 by site.

*These potential covariates apply only to the treatment arm and do not have a control arm subset.

**Table 9 T9:** 180 day follow-up CT potential covariate*

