Variable	180 Day HRCT at TLC	Baseline and 180 Day HRCT at TLC	Baseline and 180 Day HRCT at RV
Target Lobe Atelectasis Score^†^		X	X
Lobar Exclusion^†† ^(yes/no)	X		

*These potential covariates apply only to the treatment arm and do not have a control arm subset.

^†^Atelectasis Score is a continuous variable from 0 to 100% and is defined as the % volume change in the target lobe from baseline to 180 day follow-up.

^††^Lobar Exclusion will be determined by the core lab radiologists and is defined as all airways into the target lobe are occluded by valves at day 180.

**Table 10 T10:** Covariate variable derivations

**Variable**	**Definition**
RV	Residual Volume by Spirometry and Plethysmography (TLC - Max (FVC or VC))
TLC	Total Lung Capacity by Plethysmography
VC	Vital Capacity by Plethysmography
FVC	Forced Vital Capacity by Spirometry
FEV_1_	Forced Expiratory Volume in the First Second by Spirometry
Target Lobe	RUL, RLL, LUL, or LLL
RUL	RUL Target vs. Others
Density Score	Density Score by Lobe
Total Density Score	Sum of all Lobar Density Scores (including RML)
Ipsilateral DS Heterogeneity	Target - Max DS of Non-treated Lobes within Treated Lung [e.g.: RUL - Max(RML, RLL)]
Thorax DS Heterogeneity	Target DS - Max DS of All Non-treated Lobes [e.g.: RUL - MAX (RML, RLL, LUL, LLL)]
Target Lobe DS % Delta	(TLC HRCT - RV HRCT)/TLC HRCT Density Score of Target Lobe
Target Lobe Volume % Delta	(TLC HRCT Volume - RV HRCT)/TLC HRCT Volume of Target Lobe
Fissure Score	Categorical Fissure Assessment Surrounding Target Lobe
	1 = Absent
	2 = Incomplete
	3 = Complete
NETT Strata	1 = Upper-Lobe Predominance, Low Baseline Exercise Capacity*
	2 = Upper-Lobe Predominance, High Baseline Exercise Capacity
	3 = Non-Upper-Lobe Predominance, Low Baseline Exercise Capacity
	4 = Non-Upper-Lobe Predominance, High Baseline Exercise Capacity
Target Lobe Atelectasis Scores	% change in Target Lobe Volume at TLC and at RV between Baseline and 180-day HRCT
Lobar Exclusion	Yes, If all bronchial pathways to target lobe are sealed by valve(s) – adjudicated by HRCT Core Lab
Valve Combinations	1. Small ONLY
	2. Small AND Large
	3. Large Only
Large Valve	Any procedure with Only Large Valves vs. all others
Small Valve	Any procedure with Only Small Valves vs. all others

*Low Exercise Capacity by Cycle Ergometry ≤ 25 W for Women, ≤ 40 W for Men

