### Study limitations

One limitation of this study is the difficulty in performing a double-blind sham procedure study for reasons discussed earlier. As such, a potential placebo effect could influence the quality of life and exercise measurements. From the investigator's perspective the frequency of adverse events attributable to the valve will obviously be different for the control and valve cohorts. Common but potentially serious adverse events such as exacerbation frequency may be interpreted differently given the knowledge of treatment assignment. Despite attempts to standardize insertion protocol, there remains considerable variability related to delivery of general or moderate sedation anesthesia that could affect procedure time and possibly outcome. Finally, the rigid inclusion criteria and targeting algorithms utilized in this trial limit the discovery of other potentially effective emphysema treatment strategies. Given the many subtypes of emphysema, the outcome of this study may not generalize to all individuals with the disease.

The VENT study evaluates the effectiveness of endobronchial valve placement to reduce lung volume in emphysematous patients as compared to optimal medical management. Due to the similarities between this study and the NETT study of lung volume reduction surgery, efficacy and safety comparisons to those achievable with LVRS are anticipated.

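### The randomisation strata taken from NETT are not exempt from the significance screen, so stratum results would often be absent and, when shown, would exaggerate the contrast between subgroups

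*Protocol article*

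**What the plan says.** The Overview section of the protocol article states that "Patient randomization in VENT was stratified per the subgroups identified in the NETT", by treated lung region (upper or lower) and exercise capacity after rehabilitation (low or high). The same paragraph explains that the design largely follows NETT, partly because of "a goal of allowing easy comparisons between the results of the NETT and VENT". Study limitations closes by saying that "efficacy and safety comparisons to those achievable with LVRS are anticipated".

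In the Analysis section the strata have no special status. Table 8 lists NETT Strata, defined as "Randomization Stratification by Baseline Cycle Ergometry and HRCT at TLC", among the potential covariate interactions. Table 10 gives it four levels, the first being "Upper-Lobe Predominance, Low Baseline Exercise Capacity". The candidates in Tables 6 to 9 "will be subjected to a univariate screening procedure similar to that described by Hosmer and Lemeshow". After that, "Main effects and interactions with a p-value of 0.15 or less are allowed to enter a multivariate analysis". Variables with a statistically significant treatment interaction in the mixed model go on to subgroup analysis, and "univariate sub-set analysis will be performed using only those independent variables that remain in the mixed model as interactions with the treatment arm". The stated reason is to limit multiple testing. Secondary endpoints follow the same method. No level is given for significance in the mixed model, and no sentence takes the stratification factor out of the screen.

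**The concern.** Stratifying by the NETT subgroups makes them the most natural prespecified subgroups in the trial, and the ones a reader would set beside NETT. The Background reports NETT's benefit by subgroup: upper-lobe disease, and within it low exercise capacity. As written, a VENT result in those subgroups appears only after a significance test with limited power.

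Two things follow. A real difference between strata may go unreported, and a reader may take the silence as evidence of no difference. When stratum results do appear, they appear because the observed contrast was large, so that contrast overstates the truth on average. Neither effect touches the primary comparison. Both affect what VENT can say about who benefits.

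**Working it through.** **Inputs.** From the Analysis section: N = 270, allocation 2:1, SD 33.7 for FEV1 and 41.5 for the six-minute walk (6MWT, percent change), design effects of 15 and 17 points, one-sided 0.025, and an entry screen of 0.15. Not given in the article, hence assumed: stratum shares, true stratum effects, and the level of the second gate (0.05 and 0.15 are both shown).

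**The plan's own figure.** With 180 and 90 patients, SE = SD × √(1/180 + 1/90), which is 4.35 for FEV1 and 5.36 for 6MWT. Power is Φ(15/4.35 − 1.96) ≈ 0.93 and Φ(17/5.36 − 1.96) ≈ 0.89. The stated 0.90 is reproduced to within about a point on the limiting endpoint. The article states no figure for subgroups.

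**Precision within a stratum.** With four equal strata of 67.5 patients (45 EBV, 22.5 control), SE = SD × √(1/45 + 1/22.5):
- FEV1: 8.7 points, so a 95% CI of about ±17.
- 6MWT: 10.7 points, so about ±21.

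**Chance that the strata interaction passes.** This is a 3-df heterogeneity test with noncentrality λ = Σ(effect − weighted mean)² / SE². Assumed true effects are 25/15/5/5, whose mean is 12.5 with equal strata. The squared deviations sum to 156.25 + 6.25 + 56.25 + 56.25 = 275.
- FEV1: λ = 275 / 8.70² ≈ 3.63.
- 6MWT: λ = 275 / 10.72² ≈ 2.39.

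| Stratum shares | FEV1, 0.05 | FEV1, 0.15 | 6MWT, 0.05 | 6MWT, 0.15 |
|---|---|---|---|---|
| 25/25/25/25% | 33% | 54% | 22% | 42% |
| 35/45/8/12% | 26% | 46% | 18% | 36% |

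The 0.15 columns describe the entry screen alone. A stricter second gate would lower them.

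**Dependence on the assumed effects** (FEV1, equal strata, pass rate at 0.15 / 0.05):
- 20/15/15/10: 22% / 9%
- 25/15/10/5: 47% / 27%
- 30/15/15/0: 72% / 51%
- 30/15/0/0: 83% / 67%

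For FEV1, the strata pass more often than not at both levels only when the true spread is about 30 points, twice the design effect.

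**Other routes.** Table 7 lists Upper vs. Lower and Cycle Ergometry as separate candidates. With effects 25/15/5/5 and equal strata, the upper-lower gap is (25 + 15)/2 − (5 + 5)/2 = 15 points. For FEV1 that two-level interaction passes in 61% (0.15) or 41% (0.05) of trials. If exercise capacity is also tested as low versus high, at least one of the three tests passes in 73% / 49% (FEV1) and 62% / 37% (6MWT).

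**Effect of selection on the estimates.** Two-level case: 75% upper-lobe, true effects 20 (upper) and 5 (lower), true gap 15. For FEV1 the SEs are 5.0 (upper) and 8.7 (lower), so the SE of the gap is √(5.0² + 8.7²) ≈ 10.0. Simulated means among trials whose gap is significant:

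| Endpoint, level | Mean gap | Upper mean | Lower mean |
|---|---|---|---|
| FEV1, 0.05 | 26 | 22.8 | −3.4 |
| FEV1, 0.15 | 22.5 | 21.9 | −0.7 |
| 6MWT, 0.05 | 31 | 24.1 | −7 |
| 6MWT, 0.15 | 26 | 22.8 | −3.4 |

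For FEV1 at 0.05, the excess gap of about 11 points is made up of 2.8 above truth in the upper-lobe group and 8.4 below truth in the lower-lobe group. The smaller group carries most of the distortion.

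**The case against.** The gate has a stated and respectable purpose. With dozens of candidates in Tables 6 to 9, requiring an interaction before looking within subgroups is a recognised guard against spurious findings. That stands for the exploratory covariates. It does not argue against reporting estimates with intervals for one prespecified stratification factor, because estimation spends no alpha.

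The article does not contradict itself, and this stands. The comparison goal is given for the design as a whole, the closing remark on lung volume reduction surgery is at trial level, and stratified randomisation also serves balance between arms. A reader might infer that stratum results were promised and then withheld, but no sentence promises them.

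It may be said that a fuller document adds a descriptive stratum table. It might. The point here is the rule the article does state, whose wording restricts sub-set analysis to surviving interactions. The following sentence, on adjusted analyses of the remaining variables, is ambiguous and does not clearly reopen the door.

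The objection on size also stands in part. A reader might infer that NETT-subgroup results will be missing in 67–78% of trials. That is the equal-strata figure at 0.05 for the four-level factor alone. The article does not fix 0.05 for the second gate, and Table 7 offers other routes to NETT-type results.

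**Conclusion.** The concern holds in a limited form. The rule makes reporting of the randomisation strata depend on significance. Under plausible but assumed effects and shares, four-stratum results would often be absent: the interaction passes in 18–33% of trials at 0.05 and in 36–54% at the 0.15 entry screen, across the two endpoints. Larger true heterogeneity raises these rates. Competition among correlated candidates in the mixed model was not modelled and could move them either way.

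When a subgroup result is shown because it was significant, the contrast is exaggerated, by about 1.5 to 2.1 times in the two-level example (22.5/15 to 31/15). A reader might infer that every stratum estimate is biased upward. The figures do not support that: the upper-lobe FEV1 mean rises only from 20 to about 22–23, while the smaller lower-lobe group is pulled down.

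The primary intention-to-treat comparison and the success rule are unaffected. Nor does the article say that this screen governs the Major Complication Composite, so the point is confined to the efficacy endpoints. It is a worthwhile, cheap correction and no threat to the main result.

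**What to change.** Exempt NETT Strata from the screened list. State that, for FEV1 and the six-minute walk, the EBV-control difference with a 95% CI will be reported in each of the four randomisation strata, together with one strata-by-arm interaction test per endpoint, whatever the screen shows. Label this as estimation, with no claim of significance within a stratum. Keep the screen and its multiplicity rationale for all other covariates, and state the level that the mixed-model gate uses.

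The cost is a sentence or two and one table. The downside is imprecision: about ±17 points (FEV1) and ±21 (walk) with equal strata, which exceeds the design effects of 15 and 17, and wider still in small strata. A stratum holding 8% of patients would have an FEV1 interval of about ±30. These intervals show honestly how little the trial can say within a stratum. Results shown only after selection are just as imprecise, and their contrast is distorted as well.

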### Secondary outcome measures

Disease specific quality of life (as measured by St. George's Respiratory Questionnaire), exercise capacity as measured by incremental cycle ergometry, daily supplemental oxygen requirement, and dyspnea (as measured by the modified Medical Research Council (mMRC) dyspnea scale, (see Table 1) are secondary efficacy endpoints to be assessed at baseline and 180 days post randomization. Appropriate adjustments will be made to account for impact on Type I error[11].

**Table 1 T1:** Outcome measures

**Co-primary efficacy endpoints**	Mean % change in FEV_1 _and 6 MWT in the treatment group as compared to control group at 180 days post randomization.
**Primary safety endpoint**	Major Complications Composite at 180 days post randomization.
**Secondary efficacy endpoints**	Mean absolute change in: - St. George's Respiratory Questionnaire - Maximal work load as measured by cycle ergometry - Daily oxygen requirement - mMRC
**Secondary safety endpoints**	Complications (type, timing, and severity, including Kaplan-Meier survival analysis) Device-related adverse events during procedure hospitalization Device-related adverse events post discharge

Abbreviations: FEV_1 _= forced expiratory volume in one second, 6 MWT = six minute walk test, RV = residual volume, DLco = diffusion of the lung for carbon dioxide, BODE index = body-mass index, airflow obstruction, dyspnea, and exercise capacity index, EBV = endobronchial valve, mMRC = modified Medical Research Council dyspnea scale

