### Screening assessments and high resolution computed tomography (HRCT)

Consented patients began an initial medical screening to assess preliminary eligibility including demographic data, medical history, physical exam, and inclusion/exclusion criteria screening. The procedures for assessment and determination of patient eligibility are outlined in Table 2 and detailed below. Further screening included spirometry, plethysmography, diffusing capacity, exercise tolerance, and a high resolution computed tomography (HRCT) scan of the chest.

**Table 2 T2:** Screening and eligibility procedures

1.	Patient referred to study physician
2.	Patient consent obtained
3.	Screening Assessment 1: medical history, supplemental oxygen use and physical exam
4.	Determine if patient meets eligibility criteria
5.	Screening Assessment 2: electrocardiogram, spirometry, plethysmography, DLco, 6 MWT, Computed Tomography Scan, PaO_2_, PaCO_2_, arterial saturation, continine level, alpha-1 antitrypsin concentration
6.	Determine if patient continues to meet eligibility criteria
7.	Patient enters and completes pulmonary rehabilitation program
8.	Baseline measurements taken: medications, supplemental oxygen use, physical exam, electrocardiogram, spirometry, plethysmography, DLco, 6 MWT, cycle ergometry, quality of life surveys, chest x-ray, ventilation/perfusion (V/Q) scan, PaO_2_, PaCO_2_, arterial saturation, blood electrolytes, liver profile, renal profile, CBC, pregnancy test (where appropriate), and continine level
9.	Final determination of patient eligibility
10.	Randomization to Control or Treatment arm of the VENT study.

Abbreviations: DLco = diffusion of the lung for carbon monoxide, 6 MWT = six minute walk test, PaO_2 _= arterial pressure of oxygen, PaCO_2 _= arterial pressure of carbon dioxide, CBC = complete blood count.

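### The candidate covariates carried over to the secondary endpoints omit baseline SGRQ and baseline oxygen use, hold baseline mMRC only inside BODE, and assure no endpoint adjustment for its own baseline

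*Protocol article*

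**What the plan says.** The Analysis section sets out a two-stage method for the co-primary endpoints. Stage one compares change between arms "using an unpaired t-test if data are normally distributed or Mann-Whitney-Wilcoxon test if data require non-parametric testing". Stage two is a mixed model, one of whose purposes is stated as "to adjust for potential imbalances in randomization, both primary endpoints will be further tested via a multivariate model".

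The candidates for that model are named: "the potential covariates listed in Tables 6, 7, 8, 9 will be subjected to a univariate screening procedure". The entry rule is also fixed: "Main effects and interactions with a p-value of 0.15 or less are allowed to enter a multivariate analysis". No covariate's own-baseline role exempts it from the screen.

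For the secondary endpoints there is one sentence: "Secondary endpoint analyses will follow the same methodology as described above".

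Table 1 defines four secondary efficacy endpoints, each as a mean absolute change: SGRQ, maximal work load by cycle ergometry, daily oxygen requirement and mMRC. Under Secondary outcome measures, these "are secondary efficacy endpoints to be assessed at baseline and 180 days post randomization". Table 2, step 8, places supplemental oxygen use, cycle ergometry and "quality of life surveys" among the baseline measurements. Table 8 defines Baseline BODE as "BMI, FEV_1_% predicted, MMRC, 6 MWT Composite Score".

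**The concern.** For an endpoint analysed as change, the baseline value of that same measure is a natural covariate, because change depends on where the patient started. The candidate list provides for this with FEV1 and 6 MWT, the two primaries. It appears to have been carried to the secondary endpoints without the matching entries.

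Randomisation is stratified only by treatment region and exercise capacity (Methods, Overview), so the design does nothing directly to balance SGRQ, oxygen use or mMRC. If one of these differs between arms by chance, a model confined to Tables 6 to 9 cannot do for that endpoint what the plan says the model is for, or in the case of mMRC does it only in part. Precision is also given up although the baselines are already collected. This matters most for SGRQ, which the Discussion treats as one of the measures for weighing benefit against harm. The Discussion does not say the same of oxygen use or mMRC.

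**Working it through.** **Step 1: each endpoint against the tables.**

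| Endpoint | Own baseline in Tables 6–9? | Where |
|---|---|---|
| FEV1 (primary) | Yes | Table 6 |
| 6 MWT (primary) | Yes | Table 7 |
| Maximal work load (secondary) | Yes | Table 7, cycle ergometry |
| mMRC (secondary) | Only as one of four components | Table 8, Baseline BODE |
| SGRQ (secondary) | No | – |
| Daily oxygen requirement (secondary) | No | – |

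Of the four secondary endpoints, one has its own baseline listed, one has it only within a composite, and two lack it. Even the one that is listed must pass the 0.15 screen, so its adjustment is not assured.

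**Step 2: inputs for sizing the consequence.** The plan gives no figure to reproduce here. From the Analysis section: 270 patients randomised 2:1, so 180 and 90. Assumed, because the documents give no value: a correlation r between baseline and day 180 of 0.5 to 0.8, equal SDs at the two times, and a linear relation. The arithmetic uses absolute change, as in Table 1.

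**Step 3: precision.**

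- Variance of an unadjusted change score: 2(1 − r)SD².
- Variance after adjustment for own baseline: (1 − r²)SD².
- Ratio of unadjusted to adjusted: 2(1 − r)/(1 − r²) = 2/(1 + r).
- Number of adjusted patients giving the precision of 270 on unadjusted change: 270 × (1 + r)/2.
- Power after adjustment where the unadjusted analysis has 80% (two-sided 0.05): Φ[(1.96 + 0.84) × √(2/(1 + r)) − 1.96].

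| r | 2/(1 + r) | Extra variance if unadjusted | Adjusted patients equivalent to 270 | 80% power becomes |
|---|---|---|---|---|
| 0.5 | 1.33 | 33% | about 202 | about 90% |
| 0.6 | 1.25 | 25% | 216 | about 88% |
| 0.7 | 1.18 | 18% | about 229 | about 86% |
| 0.8 | 1.11 | 11% | 243 | about 84% |

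**Step 4: chance imbalance.** The standard error of a baseline difference between arms is SD × √(1/180 + 1/90) = 0.129 SD, and its 95% limit is 1.96 × 0.129 = 0.25 SD. With equal variances, the regression of change on baseline has slope −(1 − r). A baseline difference of d therefore shifts the unadjusted change difference by (1 − r)d in size. At the 95% limit:

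- r = 0.5: 0.5 × 0.253 = 0.13 SD
- r = 0.6: 0.4 × 0.253 = 0.10 SD
- r = 0.7: 0.3 × 0.253 = 0.08 SD
- r = 0.8: 0.2 × 0.253 = 0.05 SD

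**The case against.** The sentence on secondary endpoints speaks of methodology, which may mean only the sequence of test, screen and mixed model. Since the list holds the primaries' own baselines, one could expect each secondary endpoint's own baseline to be substituted. The article is condensed and the analysis plan is not shown. This keeps the intent open, but it does not remove the point: the text names particular tables and an entry rule, then carries them over without saying that anything is substituted. Under either reading, no own baseline is assured entry, because the 0.15 screen still applies.

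A reader might infer that three of the four secondary endpoints cannot be adjusted for their starting value at all. The documents do not support that. All four are change scores, so the starting value is already subtracted; what may be missing is regression adjustment for the dependence of change on baseline that remains whenever r is below 1. Nor is mMRC absent: it enters through BODE, diluted by BMI, FEV1 % predicted and 6 MWT.

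A reader might also infer that the treatment comparison is biased. Under randomisation the unadjusted comparison of change is valid. The shift in Step 4 is conditional on a chance imbalance having occurred.

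Two further cautions stand. The linear, equal-variance formula is a rough guide for a short ordinal scale such as mMRC, and for daily oxygen use. And trial success rests on the co-primary endpoints alone, so this point does not affect the trial's main conclusion.

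**Conclusion.** The point holds as a gap in the specified model for the secondary endpoints. As written, the SGRQ and oxygen models cannot regression-adjust change for baseline, the mMRC model can do so only through a partial proxy, and the work-load model does so only if its baseline passes the screen. This falls short of the model's stated purpose of correcting imbalance, although all four measures are taken at baseline.

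The cost is efficiency and protection against chance imbalance; validity is not at stake. The size given in the working depends on an assumed r, equal variances and linearity, and it shrinks as r rises. Adopting the adjustment would be a worthwhile improvement at almost no expense.

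**What to change.** In the Analysis section, state that the multivariate model for each secondary endpoint includes that endpoint's own baseline (SGRQ, maximal work load, daily oxygen requirement or mMRC) as a forced covariate, outside the univariate screen. State also that the resulting baseline-adjusted treatment effect will be reported with the initial unadjusted test. This keeps the plan's order of analyses.

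If substitution of own baselines was already intended, the same sentence makes it explicit. The cost is a sentence or two in the plan and one covariate per model; no additional data collection is needed.
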